#### Statistical power

The total number of patients planned investigated are *n* = 630 SOT recipients. We have performed power calculations to ensure adequate power:

#### Flow cytometry

Fernandez-Ruiz et al. [32] have found that a low NK-cell count (< 0.050 × 10^3^ cells/μL) at month one post liver-transplantation was associated with a greater risk of opportunistic infections at month one to six post transplantation. To detect such likely-hood ratio with α = 0.05 and power(β) = 0.80 for the incidence rate of 0,09 OI/1000 days vs. 0,58 OI/1000 days a total of *n* = 28 SOT recipients is required.

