### Complete immunological profile

In all participants we will collect blood samples before the transplantation (either while the patient is on waiting list or just before the surgical procedure and before the initiation of immunosuppression) and 7–14 days, 3 months, 6 months, 12 months and 24 months post-transplantation.

The complete immunologic profiling includes concomitant characterization of immune phenotypes and circulating plasma biomarkers and determination of immune function (Table 1). This immunologic profile is developed in collaboration with experts in infectious diseases, immunology and clinicians taking care of SOT recipients at Rigshospitalet, PERSIMUNE, MATCH and Milieu Intérieur, Institute Pasteur, Paris, France, the latter taking advantage of their experience with immunologic profiling in The Healthy Human Global Project [24–29].

**Table 1 Tab1:** Method and data output of the immunological profile. Description of blood sample collection, laboratory analysis and data-output from the immunological profile, consisting of immune phenotype (flow cytometry), immune function (TruCulture®) and circulating plasma biomarkers

	Method	Data output
Immune phenotype (flow cytometry)	3 ml EDTA anticoagulated whole blood. The whole blood is analyzed on a Navios flow cytometer (Beckman-Coulter) within 24 h after blood sampling.	Proportion and intensity (mean fluorescence intensity, MFI) of antigens (most designated clusters of differentiation, CD) on the blood immune cells investigated in the flow cytometry panel.
Immune function (TruCulture®)	9 ml lithium heparin anticoagulated whole blood. The whole blood is transferred to individual TruCulture® tubes 60 min after blood sampling. After 22 h incubation at 37 °C, the TruCulture® supernatant is harvested and aliquoted to cryo tubes and frozen at − 20 °C for later thawing and bulk analysis of soluble immune activation products. The mRNA in the TruCulture® cell pellet is stabilized by Trizol and frozen at − 80 °C for later bulk analysis of mRNA expression level of stimulated immune proteins.	TNF-α, IL-1β, IL-6, IL-8/CXCL8, IL-10, IL-12p40, IL-17A, IFN-γ Expression levels of the immune protein mRNA included in the multiplex assay will be calculated and reported.

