#### Immune phenotype

Immune phenotyping will be conducted in a subset of participants (*N* = 100–630 depending on funding). The flow cytometry panel will be designed to reveal the immune phenotypes of critical developmental and/or activation stages of immune cells to capture deviated maturation patterns, acute/chronic activation, exhaustion, migration/trafficking potential and deviated expression of immune checkpoint markers.

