### Statistics and power calculation

#### Statistics

The data from the trial will be analyzed both separately for each patient category using classical statistical analyses and merged across the different patient categories and sampling time-points using computational modelling.

The data will be analyzed by classical statistical analyses i.e. descriptive statistics will be calculated for endpoints with summary statistics for continuous variables including n, means with standard deviation and medians with min/max or inter quartile ranges and summary statistics for categorical variables including n and proportions. Differences in continuous variables (including calculated delta-values) within groups between time-points will be analyzed by paired tests (t-test, Wilcoxon-signed rank test), mixed models or repeated measurements analysis (ANOVA, ANCOVA, Friedman), the latter followed by post hoc pairwise comparisons. Differences across different patient-groups or responses will be analyzed by two-sample t test or Mann-Whitney U test. Differences in categorical values will be analyzed by Chi-square tests or Fishers exact test as appropriate and McNemars test for changes over time.

The predictive value of immunologic variables or categorized immunologic variables for the endpoints will be analyzed by survival statistics including Kaplan-Meier plots and log rank test and Cox proportional hazards models. Furthermore, linear and logistic regression models will be applied to investigate the predictive value of immunologic variables for continuous and categorical endpoints. Analyses may be stratified by underlying disease/baseline patient characteristics, and odds ratios of outcomes among patients with an immunologic variable below or above a certain threshold will be estimated by logistic regression analyses adjusted for relevant covariates. The sensitivity, specificity, positive- and negative predictive value of specific immunologic variables or patterns for outcome will be calculated. *P*-values < 0.05 will be considered significant.

Furthermore, computational modelling of data applying a bioinformatics approach will be conducted by e.g. unsupervised learning to reveal patterns in the immunologic variables and profile predictive for the endpoints (data mining, clustering and/or Bayesian models, principal component analyses (PCA)).

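### The flow-cytometry sample size of 28 enters infection rates per 1000 days as if they were percentages; over the stated window about 290 patients are needed for 80% power

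*Protocol article*

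**What the plan says.** The Statistical power section puts the planned total at 630 recipients and offers three calculations as assurance of adequate power. The one for flow cytometry rests on a published finding that a low NK-cell count "at month one post liver-transplantation was associated with a greater risk of opportunistic infections at month one to six post transplantation". Its inputs are given "for the incidence rate of 0,09 OI/1000 days vs. 0,58 OI/1000 days", its error rates as "To detect such likely-hood ratio with α = 0.05 and power(β) = 0.80", and its result is a total of 28 recipients. It does not state sidedness, the share of patients with a low count, person-time, or a conversion from rate to risk.

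Two other places bear on how the figure is used. Under Immune phenotype, "Immune phenotyping will be conducted in a subset of participants", with a range of 100 to 630 that depends on funding. Under Complete immunological profile, post-transplant samples are taken at 7–14 days and then at "3 months, 6 months, 12 months and 24 months post-transplantation".

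**The concern.** A rate of 0.58 per 1000 days is not a risk of 58%. Over a window of about five months it is a risk of roughly 8%. A total as small as 28 is plausible only if the two rates were entered as proportions.

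The size of the phenotyping subset is still open. Set against a requirement of 28, the floor of 100 looks more than three times as large as necessary. If the true requirement is about ten times 28, a subset near that floor would have a poor chance of detecting the effect the paragraph names, and a reader deciding how much phenotyping to fund would be misled in the favourable direction.

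**Working it through.** **Inputs.** From the Flow cytometry paragraph: rates λ₁ = 0.00009 and λ₂ = 0.00058 per day, window month one to month six (taken as 150 days; 152 gives nearly the same), α = 0.05, power 0.80. Assumed because not stated: two-sided test, 1:1 split, constant rates, no loss to follow-up. The first two assumptions are the ones that reproduce the printed figure.

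**1. Reproduce 28.** Pooled two-proportion formula, per group:

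n = [1.960·√(2p̄(1−p̄)) + 0.842·√(p₁(1−p₁) + p₂(1−p₂))]² / (p₂−p₁)²

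With p₁ = 0.09, p₂ = 0.58, p̄ = 0.335: (1.308 + 0.480)² / 0.2401 = 13.3, so 14 per group and **28 in total**, an exact match. The same formula gives the protocol's other two sizes exactly: 486 for 64% vs 75% at power 0.75 (plasma biomarkers) and 24 for 6.6% vs 58% at power 0.80 (TruCulture). Those inputs are true percentages; the flow-cytometry inputs are not.

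**2. Can 9% and 58% be risks at some follow-up time?** −ln(0.91)/0.00009 ≈ 1048 days and −ln(0.42)/0.00058 ≈ 1496 days. The two times differ, and both far exceed the 150-day window and the 24-month sampling schedule.

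**3. Convert rates to risks.** 1 − exp(−0.00009 × 150) = 1.34%; 1 − exp(−0.00058 × 150) = 8.33%.

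**4. Corrected size, same formula.** With p̄ = 0.0484: (0.595 + 0.252)² / 0.0699² = 146.6, so 147 per group, **294 in total**. At 152 days (1.36% vs 8.44%) it is 145 per group, **290 in total**.

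**5. Other methods, two-sided, 1:1, 150 days.**
- Poisson rate difference: (1.960 + 0.842)² × 0.00067 / 0.00049² / 150 = 146 per group, about 292.
- Log rate ratio (Wald): 193.5 per group, about 387.
- Schoenfeld: 4 × 7.85 / (ln 6.44)² = 9.04 events; divided by a mean risk of 4.84%, about 187 (207 if rounded up to 10 events).
- One-sided pooled formula: 232.

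**6. Longer time at risk** (pooled formula, rates held constant): 122 in total for one year, 62 for two years. Neither comes down to 28.

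**7. Share with a low NK count** (pooled formula, 150 days): about 568 at 10%, 287 at 40%, 293 at 50% before rounding up per group, 380 at 70%.

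**8. Power over 150 days, 1:1.** At n = 28, expected events are 14 × 150 × (0.00009 + 0.00058) = 1.4.

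| Total N | Exact conditional Poisson | Pooled normal approximation |
|---|---|---|
| 28 | 0.1% (Fisher: 0.4%) | 13% |
| 100 | 17% | 37% |
| 180 (all liver recipients) | 49% | 59% |
| 630 | 99% | 98% |

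The exact test is conservative with few events, and the normal approximation is optimistic there, so each power is best given as a range.

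**The case against.** The strongest reply is that 28 drives nothing. Enrolment is 630, the phenotyping subset is set by funding, and the plasma-biomarker calculation already asks for 486, more than the corrected figure. The study is observational, and this is one illustrative effect of three. That limits the damage, but the section presents these calculations as ensuring adequate power, and the printed size does not follow from the printed inputs.

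A second reply is that infections are counted over one year in the primary endpoint. If the same rates held for 365 days, power would be about 68–72% at N = 100 and 93–94% at N = 180. This is fair as a sensitivity, but the paragraph fixes its window at months one to six, and nothing in it says the rates persist. Even then 122 patients are needed, not 28.

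Three stronger readings are tempting and not supported:
- *That the flow-cytometry plan as a whole is underpowered.* At 630 the power is 98–99%.
- *That any departure from a 1:1 split makes matters worse.* A 40% low-count share needs slightly fewer patients by the pooled formula (287 vs 293); only markedly unequal splits need many more.
- *That the calculation fails because opportunistic infection is not a named endpoint.* It is not named as such, but CMV infection, pneumonia and a composite of viral, bacterial or fungal infection or rejection are listed. How far these overlap with the cited definition cannot be checked from the article.

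The sampling-time mismatch (a month-one predictor, with samples at 7–14 days and 3 months) is real but separate, and the arithmetic error does not depend on it.

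**Conclusion.** The figure of 28 is wrong by about a factor of ten, in the favourable direction. It results from using events per 1000 days as proportions. For the stated rates and window, 80% power needs about 290 patients in total, given a two-sided test, a 1:1 split, constant rates and complete follow-up. Across methods at 1:1 the range is about 190 to 390; with only 10% of patients in the low-count group it is about 570.

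The practical consequence is confined to the low end of the phenotyping range. A subset of 100 is underpowered for this effect over months one to six, and so is an analysis of the 180 planned liver recipients alone, the organ group in which the effect was reported. The full cohort is ample.

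**What to change.** Replace 28 with the person-time result: about 290 in total for 0.09 vs 0.58 per 1000 days over months one to six, stating the test, sidedness, assumed split and follow-up. Alternatively, state the power the funded subset delivers as a range with the method named, for example 17% (exact conditional Poisson) to 37% (pooled normal approximation) at N = 100. In the same paragraph, refer to a sampling time the trial has, since there is no month-one sample.

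The cost is one recalculated paragraph and a less favourable figure. Planned enrolment of 630 already exceeds the corrected size.

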#### Plasma biomarkers

Several studies have reported that plasma sCD30 predicts infectious complications and acute rejection [33, 34] in kidney transplant recipients with a 64% vs. 75% 5-year graft survival in patients with high vs. low sCD30 levels [34]. To detect such likely-hood ratio with α = 0.05 and power(β) = 0.75, a total of *n* = 486 patients is required.

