### Study-participants

To be eligible for the study the participant must be a minimum of 18 years of age and have a planned kidney-, heart-, lung-, liver- or pancreas-transplant and be able to provide informed consent. Study participation is strictly voluntary.

During a three-year-period we aim to include 630 SOT recipients: *n* = 270 kidney-, *n* = 90 lung-, *n* = 45 heart-, *n* = 180 liver-, and n = 45 pancreas recipients from Rigshospitalet, University of Copenhagen [1]. A study nurse is employed to ensure adequate participant enrolment and complete follow-up.

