#### Circulating plasma biomarkers

Circulating levels of cytokines will be measured in a subset of participants (*N* = 100–630 depending on funding). The panel will include immune or inflammatory cytokines, autoantibodies against cytokines, chemokines, growth factors, adhesion molecules that injury/death products reflecting the magnitude of immune cell- and/or tissue activation and/or injury in vivo will be assessed by measuring the biomarkers. The soluble plasma biomarkers as well as autoantibodies against these will be measured by high-throughput multiplex platforms like Luminex® or Meso Scale Discovery (MSD®), by NanoString® and by enzyme linked immunosorbent assay (ELISA).

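### The plasma-biomarker calculation (486 patients, 75% power) does not secure the claimed adequate power: it rests on 5-year kidney graft survival, and as few as 100 participants may be assayed

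*Protocol article*

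**What the plan says.** The Statistical power section of the protocol article introduces three assay-specific calculations with the statement "We have performed power calculations to ensure adequate power". The one for plasma biomarkers starts from reports that "plasma sCD30 predicts infectious complications and acute rejection [33, 34] in kidney transplant recipients" and takes as its effect "64% vs. 75% 5-year graft survival in patients with high vs. low sCD30 levels". It continues "To detect such likely-hood ratio with α = 0.05 and power(β) = 0.75", and concludes that "a total of *n* = 486 patients is required".

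Other sections fix what the study will have:

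- **Study-participants:** "During a three-year-period we aim to include 630 SOT recipients", made up of 270 kidney, 90 lung, 45 heart, 180 liver and 45 pancreas recipients.
- **Circulating plasma biomarkers:** "Circulating levels of cytokines will be measured in a subset of participants", with N given as 100 to 630 depending on funding.
- **Complete immunological profile:** one sample before transplantation and one at 7 to 14 days, then "3 months, 6 months, 12 months and 24 months post-transplantation".
- **End-points:** the primary endpoints are infections and graft rejection within 1 year. The secondary endpoint is a composite of infection or rejection at 28 days, 90 days and 2 years. Graft survival is not listed.
- **Statistics:** analyses are planned both separately by patient category and merged across categories.

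**The concern.** A power statement is useful only if the population, outcome, time horizon and number analysed are those of the study. Here all four differ or are left open. The effect comes from kidney recipients, who are fewer than half of the cohort. The outcome is graft survival, which is not an endpoint. The horizon is 5 years, while sampling and endpoints stop at 2. The number assayed may be anything from 100 to 630, and much of that range lies below the 486 that the protocol itself calls for.

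The study aims to learn whether immune profiling predicts infection and rejection, and to build risk models that would feed later randomised trials. If plasma is assayed in a small subset, a null result for a marker with an effect of the assumed size would say little. A reader relying on the power statement could take it as evidence of no association.

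**Working it through.** **Inputs.** From the Plasma biomarkers paragraph: p1 = 0.64, p2 = 0.75, α = 0.05, power 0.75, total 486. From Study-participants: 270 kidney recipients of 630. From Circulating plasma biomarkers: 100 to 630 assayed. The protocol states neither sidedness nor group split; two-sided and 1:1 are inferred because they reproduce the stated figure.

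**Step 1: reproduce 486.** With the pooled two-proportion formula,

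n per group = [z(1−α/2)·√(2·p̄·q̄) + z(power)·√(p1·q1 + p2·q2)]² / (p1 − p2)²

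- p̄ = (0.64 + 0.75)/2 = 0.695, so √(2 × 0.695 × 0.305) = √0.42395 = 0.6511
- √(0.64 × 0.36 + 0.75 × 0.25) = √0.4179 = 0.6465
- n = (1.960 × 0.6511 + 0.6745 × 0.6465)² / 0.11² = 2.932 / 0.0121 = 242.3, rounded up to 243

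The total is 2 × 243 = 486, an exact match.

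**Step 2: power for the same contrast at the numbers in the protocol.** Rearranging, with n per group,

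power = Φ[(0.11·√n − 1.276) / 0.6465]

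| Total N | n per group | Argument of Φ | Power |
|---|---|---|---|
| 100 (lower end of assayed range) | 50 | −0.771 | 22% |
| 270 (all planned kidney recipients) | 135 | 0.003 | 50% |
| 486 (stated requirement) | 243 | 0.678 | 75% |
| 630 (whole cohort) | 315 | 1.046 | 85% |

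The 22% assumes that all 100 are kidney recipients or that the effect is common to all organs. If the 100 followed the planned organ mix, about 100 × 270/630 = 43 would be kidney recipients, and a kidney-only comparison would have about 12% power. The 75% and 85% figures go beyond the 270 kidney recipients, so they need the kidney effect in liver, lung, heart and pancreas recipients as well.

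**Step 3: sensitivity to the split.** If one quarter of patients had high sCD30 (an assumption; the protocol gives no proportion), power would be about 20% at 100, 42% at 270, 64% at 486 and 75% at 630.

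**Step 4: sensitivity to the horizon.** Step 2 still grants a 5-year outcome. Under a constant hazard (an assumption), 2-year graft survival would be 0.64^(2/5) = 83.7% against 0.75^(2/5) = 89.1%. Power would then be about 12% at 100, 26% at 270 and 52% at 630. This only shows how much the horizon matters. It is not power for any protocol endpoint.

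**The case against.** The protocol asks for 486 patients, not 486 kidney recipients; it plans 630, and the Statistics section provides for analyses merged across organs. If everyone is assayed, power for this contrast is 85% with equal groups and still 75% with a 1:3 split. The other two calculations also borrow published contrasts as benchmarks, and the TruCulture® one uses oncology patients because transplant data were lacking. The sCD30 paragraph mentions infectious complications and acute rejection, so graft survival can be read as a proxy effect size and not as a planned analysis. The study is observational, and no treatment decision rests on this number.

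Much of this stands. A reader might infer that the sample size is miscalculated, that the cohort is simply too small, or that the authors intend a 5-year graft-survival analysis they cannot run. The documents support none of these. The choice of 75% power, where the other two calculations use 80%, is disclosed and is not an error.

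The objection does not rescue the adequate-power statement. The merged reading needs at least 486 assayed, which is 486/630 = 77% of the cohort, while the protocol allows 100. It also needs a common effect across organs, which is nowhere stated. Analyses by patient category are planned too, so the 270 figure describes an intended analysis. Calling the contrast a proxy also does not turn 75% power for 5-year graft survival into power for infection or rejection within 1 year.

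**Conclusion.** Wrong as written; should be fixed. The figure of 486 is correctly computed, but the design does not secure the power attached to it, and the outcome and horizon behind it are not those of the protocol. For the stated contrast with equal groups, power ranges from about 22% (100 assayed) to 85% (all 630), with 50% in the 270 kidney recipients. The 75% claimed is reached only at 486 or more assayed, under an unstated common effect across organs.

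These figures rest on a two-sided test and an equal split; an unequal split lowers them. They all concern 5-year graft survival, so they show that the claim is not secured. They do not estimate the study's power for its own endpoints, which this calculation leaves unknown. It would also go too far to say that plasma results will mostly be false negatives: the low figures apply to this one contrast, and larger marker effects would be easier to detect.

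**What to change.** In Statistical power and its Plasma biomarkers paragraph:

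1. Withdraw the adequate-power statement for plasma biomarkers, or qualify it by the number actually assayed.
2. Replace the 5-year graft-survival contrast with one for a protocol endpoint: infection within 1 year or rejection within 1 year. State the assumed event rates, the group split and the sidedness.
3. Show power across the 100 to 630 assayed range for the merged cohort, with the assumption of a common effect across organs written out, and separately for the kidney recipients (up to 270).

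Reprinting the 50% or 22% above would not be enough, because those are still figures for graft survival.

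The cost is some recalculated text and a less favourable stated figure. No change to enrolment or sampling is needed.

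Case-cohort selection of the frozen plasma may look like a way to protect power under limited funding, but it does not work at the low end. If the rejection rates in the Background are applied at 1 year (an assumption, since no time window is given), the planned numbers yield 0.24 × 270 + 0.60 × 90 + 0.56 × 45 = 144 rejections. Liver adds 0.27 to 0.46 × 180 = 49 to 83, giving about 193 to 227 in total. That exceeds 100 before pancreas recipients, infections or any subcohort are counted.

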#### TruCulture®

To our knowledge, TruCulture® has not been used to investigate SOT recipients. In oncologic patients undergoing neoadjuvant radio- and/or chemotherapy before surgery, low IL-12 production in LPS stimulated whole blood cultures predicts increased sepsis-related mortality (58% vs. 6.6%) [35]. To detect such likely-hood ratio with α = 0.05 and power(β) = 0.80, a total of *n* = 24 patients is required.

## Discussion

The overall outcome of solid organ transplantation is largely defined by adverse events such as infections and rejections [4–8], and optimal dosage of immunosuppression is of utmost importance. Our general hypothesis is that an improved understanding of the immune function in SOT recipients will lead to an improved management of immunosuppressive therapy, fewer infections and rejections, and improved patient outcomes.

The ability to use functional assays to determine immune function to guide management of immunosuppression has been limited due to time-consuming and expensive assays. However, recently several commercially available functional assays have become available. The ImmuKnow® (Cylex, USA) is an FDA approved functional test for cellular immune function. The principle of the test is measuring intracellular adenosine triphosphate (ATP) production in CD4 + -cells upon whole blood stimulation with phytohemagglutinin (PHA) [15]. Although the technique is promising, many of the studies conducted with ImmuKnow® have limitations including retrospective design, small number of recipients, single measurement and/or low follow-up time, and results so far are conflicting [12–14, 16–23]. One promising randomized controlled study by Ravaioli et al. found that immunosuppression dosed according to results of serial testing with ImmuKnow® increased 1-year patient survival and lowered the incidence of infections in liver transplant patients [11]. Another currently available functional test of cellular immune function is the QuantiFERON®-monitor (QIAGEN). This assay is based on measuring INF-γ released after whole blood stimulation with innate (R848) and adaptive (CD3) stimulants [36]. Mian et al. have investigated 137 SOT recipients with the QuantiFERON®-monitor 1, 3 and 6 month post-transplantation and prospectively recorded infections. They found that INF-γ-levels were lower in patients that developed infections, and that a INF-γ-level < 10 IU/mL increased the likelihood of subsequent infection by 2- to 3-fold [10].

The TruCulture® is a novel functional immune assay that will provide complex information about the immune function [24]. TruCulture® was developed at the Institut Pasteur, France, with the purpose to be incorporated in the *Milieu Intérieur*-project, which is a large-scale study of 1000 healthy French adults [37]. In the ImmuneMo:SOT study the TruCulture® consists of four carefully chosen stimuli, mimicking fungal, bacterial and viral presence, acting through different TLR pathways. Furthermore, we have chosen 8 cytokines (TNF-α, IL-1β, IL-6, IL-8/CXCL8, IL-10, IL-12p40, IL-17A, IFN-γ) as readout providing a broad and representative image of the immune function. We expect this functional assay to provide much needed information about the global immune function of the SOT-recipients.

This ImmuneMo:SOT study is a non-interventional, observational, prospective study. The primary aim is to generate new knowledge about the immune function in SOT recipients and to link this information to risk of infections and rejections. When combining classical statistics and computational bio-informatic approaches to the data generated, it is expected that the study will be able to generate prediction models that can be used to design a treatment program using personalized medicine. Other ImmuneMo studies including other groups of patients undergoing immune modulating interventions are underway (patients treated with biological treatments, hematopoietic stem cell transplantation recipients, HIV-infected patients, patients with cancer, and patients with severe bacterial infections). Furthermore, a collaboration with Milieu Intérieur will provide the boundaries for the immune function in healthy individuals.

The major strength of this study is the complete immunological profiling that will be conducted in a large number of SOT recipients prior to and after transplantation and across organ types. The immunologic profile is developed in collaboration with the *Milieu Intérieur Consortium*, Institute Pasteur, Paris, France. This consortium initiated in 2012 a large cross-sectional healthy population-based study, to assess factors underlying immunological variance within the general healthy population. They have enrolled 1000 healthy Western-European adults; 500 women and 500 men, consisting of 100 study-participants of each sex in each of 5 age-groups from 20 to 29, 30–39, 40–49, 50–59 and 60–69 year. The study-participants was (among others) assessed with a deep immunological and genetic investigation, including the use of TruCulture® [25]. This provides us a unique opportunity to compare the immune function of our study-participants to healthy controls.

Another strength, and a precondition for the feasibility of this study, is that all Danish residents are provided with a unique 10-digit personal identification number by the The Civil Registration System. This number is registered at all contacts with the health care system and allows for accurate linkage with the clinical information from the PERSIMUNE data repository.

A weakness of the study is the single-center design. The patients recruited at one geographical locality and may not be representative for patients from other geographical areas. However, as Rigshospitalet is the largest center for transplantation in Denmark and the only center in Denmark for liver and lung transplantation, it does provide a unique opportunity to perform this study and it is realistic to include patients as described.

In conclusion, there is a need for an improved understanding of immune function in SOT recipients to target the constant challenge of balancing the immunosuppression to avoid both infections and rejections.

This project has brought together the competences of many experts, including expertise within infectious diseases, immunology, and transplantation medicine. We hypothesize that the full immunologic profile, consisting of both immune phenotyping, circulating biomarkers and immune function, will provide important knowledge about the effect of organ transplantation and immunosuppression on the recipients’ immune function. And that this knowledge can be used to identify SOT recipients at excess risk of infections and rejections.

If the study is successful, the study group will use the results to design a randomized clinical trial to test personalized immunosuppressive regimes according to the recipient’s individual immunological profile. In the future both initial immunosuppression and monitoring of immunosuppression might be based on the personal immune profile as proposed in this study.

